#### Contributing centers

The launch of the EHE prospective clinical registry was shared with all the reference institutions belonging as full members or associated partners to EURACAN sarcoma domain (63 institutions across Europe).

The project was also opened to EU institutions not belonging to EURACAN and extra-EU institutions. In this case, in order to ensure an adequate degree of expertise in the disease, the institutions interested in joining the registry were asked to provide the number of new EHE cases (molecularly confirmed) seen each year over 3 years (2020-2021-2022) and a threshold of at least 20% of EHE national incident cases was selected for participation.

As a result of this process, 21 institutions joined the registry in September 2023, 17 of which belonging to EURACAN, from 10 countries.

### Inclusion criteria

New patients managed by the contributing centers with a pathological EHE diagnosis performed or verified by an expert sarcoma pathologist starting from 1 December 2023 onwards and to be performed within 6 months from the registrationMolecular confirmation of the diagnosis (*WWTR1-CAMTA1* or *YAP1-TFE3*)Adult patients (aged ≥ 18 years)

### Outcomes are listed per registry objectives

EHE population and diseases characteristics at diagnosis (M/F ratio, average age, proportion of Charlson Comorbidity index, ECOG performance status, distribution of primary site and disease extension) [4]EHE natural history (cumulative incidence of local recurrence and distant metastases per different EHE extension; description of progression patterns: site of metastatic spreading, number and site of new lesions, evolution of known lesions, presence and features of serosal involvement, time to local progression or distant metastases; overall and progression free survival) [4,7]Treatment Effectiveness (overall response rate, by RECIST1.1 and according to clinical judgment, competitive cumulative incidence of local recurrence and distant metastases, disease-free survival, overall survival)Identify Prognostic and predictive factors: overall and progression free survival and treatment responseDescription of treatment pattern and quality of care: percentage of patients treated according to Consensus paper recommendations.

#### Sample size

This is an observational clinical prospective registry which implies a long-term data collection lasting until all the registry objectives are met. Considering that we expected 10 centers in Italy (more than 30 cases per year), 1 centre in United Kingdom (more than 10 cases per year), 1 centre in Poland (about 5 cases per year), 1 centre in Germany, Spain, France, Norway, Denmark, Sweden, Austria and The Netherlands (about 3–5 cases on average each centre per year), assuming that the maximum number of expected cases will be recorded in each centre we envision about 100 patients with an EHE yearly. The already established collaboration and participation of EHE patient’s associations involved in the project will help in promoting the registry and fostering accrual. The precision of estimates of a categorical endpoint (e.g. proportion) or a continuous endpoint, respectively in terms of width of two-sided 95% Confidence Interval (CI) using the Simple Asymptotic method or in form of normal distribution for means, is based on the sample size achieved in different years during the data collection. For example, a sample size of 200 patients (e.g. EHE cases in 2 years) will achieve a maximum width of 95% CI of 0.14 (i.e. estimated proportion +/- 7%). For continuous endpoints, a sample size of 200 patients will achieve a maximum width of 95% CI of 0.28*SD (i.e. estimated mean +/- 0.14*SD, where SD = Standard Deviation).

Table 1 reports the precision of the estimates for categorical and continuous endpoint under different sample size.

**Table 1 pone.0308387.t001:** Precision of the estimates expressed as 95% Confidence Interval (CI) for categorical and continuous endpoint accordingly to different sample size.

	Categorical endpoint		Continuous endpoint	
Target sample size	max 95% CI	Width of 95% CI	max 95% CI	Width of 95% CI
350	Estimate +/- 0.05	0.10	Estimate +/- 0.10*SD	0.20*SD
300	Estimate +/- 0.06	0.11	Estimate +/- 0.11*SD	0.22*SD
250	Estimate +/- 0.06	0.12	Estimate +/- 0.12*SD	0.24*SD
200	Estimate +/- 0.07	0.14	Estimate +/- 0.14*SD	0.28*SD
150	Estimate +/- 0.08	0.16	Estimate +/- 0.16*SD	0.32*SD
100	Estimate +/- 0.10	0.20	Estimate +/- 0.20*SD	0.40*SD
70	Estimate +/- 0.12	0.24	Estimate +/- 0.23*SD	0.46*SD

To calculate the sample size for the analytical questions involving several different variables, ad hoc analysis plans will be needed.

#### Data collection and storage

The registry is federated thus, data are stored by the health care providers contributing to the registry. At the local level, data are pseudonymised.

### Data analyses

Statistical analyses will be performed based on a study protocol. Queries will be developed, in collaboration with clinical experts, to interrogate the EURACAN EHE registry to generate the descriptive statistics and relevant information needed to plan the analyses envisaged by the study protocol. Queries may include general description of the characteristics of the patients with EHE (M/F ratio, average age, primary site distribution, disease extension, progression patterns etc.) Due to the nature of the registry, supplementary statistical analysis plans are envisioned to reply to specific research questions (e.g. identification of prognostic/predictive factors) arising over time.

Here we report a general data analysis plan based on the objectives of the registry.

#### Data analyses plan

The data analyses will include descriptive statistics and analytical analyses. Descriptive statistics will be used to reconstruct the natural history of EHE (e.g. cumulative incidence of local recurrence and distant metastases, proportion of site of metastatic spreading, number and proportion of site of new lesions, evolution of known lesions, presence and features of serosal involvement, time to local progression or distant metastases etc.) and to report indicators about quality of care (e.g. description of staging procedures, description of treatment pattern, etc.).

Multivariable Cox’s proportional hazards model and Hazard ratios (HR) for all-cause or cause-specific mortality will be used to determine independent predictors of overall survival, recurrence and progression. Variables to include in the multivariable regression model will be selected based on the results of univariable analysis and using Information Criteria, such as Akaike Information Criterion. According to the specific research question the role of potential confounders and effect modifiers will be evaluated. Sensitivity analyses will be performed to estimate the potential impact of confounders. Statistical interactions between predictors and the variable will be tested to detect potential effect modifiers and stratified analyses will be performed in case of presence of any effect modifiers.

To assess treatment effectiveness, propensity score adjustment will be applied to multivariable models to remove bias due to real world nature of the registry.

High proportion of missing data threaten the validity of the inferences/prognostic models. Thus, a maximum of 10% of missing data will be allowed and missing data will be imputed using strategy such as unconditional/conditional mean or expectation maximum. To minimize missing information, in addition to the prospective nature of the registry, summary lists of information to be collected during clinical visits and including all the pathological details required for diagnosis were shared with all centers.

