○ Age at diagnosis, gender, hormonal status (for females), performance status○ Disease extent at presentation, disease size (for primary localized tumours) and disease site [4,7,10,11]○ Signs and symptoms at presentation and during follow up, including tumour-related pain, systemic symptoms (such as temperature, asthenia, anorexia, weight loss, night sweating) and limb edema [7]○ Anaemia and fibrinogen increase [12]○ Radiological features (including serosal involvement and / or effusion) [6,7]○ Pathological features (including necrosis, mitoses, nuclear pleomorphism) [10,13]○ Molecular features (including molecular translocations, *WWTR1-CAMTA1* vs *TFE3-WWTR1* vs others) [11,14,15]To describe treatment pattern and adherence to consensus paper recommendations on EHE clinical management (including diagnostic ascertainment, treatment, follow-up) [4]

To generate hypotheses on potential risk factors: demographics, sex, medical history (allergy, previous malignancies, immune-mediated diseases and previous immunosuppressive therapies, hormonal influence).

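### The missing-data strategies named for the Cox and propensity-score models include unconditional mean imputation, carry no imputation uncertainty forward, and sit beside a 10% limit with no unit or consequence

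*Protocol article*

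**What the plan says.** All of the relevant text is in the Data analyses plan section of the protocol article.

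- **Rationale and limit.** The section opens the topic with "High proportion of missing data threaten the validity of the inferences/prognostic models" and concludes that "a maximum of 10% of missing data will be allowed". It does not say whether the 10% applies to a variable, a patient, a model or the whole dataset, or what happens above it.
- **Method.** "missing data will be imputed using strategy such as unconditional/conditional mean or expectation maximum". The text does not restrict this to covariates.
- **Where the completed data go.** Multivariable Cox models "will be used to determine independent predictors of overall survival, recurrence and progression". For treatment effectiveness, "propensity score adjustment will be applied to multivariable models to remove bias due to real world nature of the registry".
- **Variable selection.** Covariates are "selected based on the results of univariable analysis and using Information Criteria, such as Akaike Information Criterion". Missingness plays no part in that rule.
- **Sensitivity analyses.** The one stated aim is confounding: "Sensitivity analyses will be performed to estimate the potential impact of confounders".

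The candidate factors in the registry objectives (Introduction) include laboratory values ("Anaemia and fibrinogen increase") and categorical factors such as disease site, serosal involvement and fusion type.

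**The concern.** The concern is with the methods the plan names, not with detail left to a later document. An unconditional mean ignores the patient's other covariates. When the filled variable is a confounder, adjustment fails in exactly the imputed rows, which works against the plan's own aim of removing bias. A mean is also not a possible value for a categorical factor: an average of disease sites means nothing, and an average of a yes/no serosal-involvement code is a fraction that no patient can have. The same holds for fusion type, although that should seldom be missing because molecular confirmation is an inclusion criterion.

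Filling in one value per gap and analysing it as observed also carries no imputation uncertainty into the standard errors, and nothing the plan names does so.

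The 10% limit leaves the analyst without a rule once it is passed, so the choice could be made after the data are seen. The Introduction and Discussion want the results to inform treatment, to serve as an external control and to support discussion with regulators.

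**Working it through.** **1. The plan's own precision figure.** The Sample size section gives a maximum 95% interval width of 0.14 for a proportion at n = 200. Check: 2 × 1.96 × √(0.25/200) = 0.139. For a mean, 2 × 1.96 × SD/√200 = 0.277 SD, stated as 0.28 SD. The other rows of Table 1 agree within rounding. These figures assume complete data.

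**2. Simple means and proportions.** Let a fraction m be missing completely at random and filled with the observed mean.

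- Complete-case SE = s/√(n(1−m)).
- After filling, the SD shrinks to s√(1−m) and n is counted in full, so SE = s√(1−m)/√n.
- Ratio = 1−m, which is 0.90 at m = 0.10.
- Actual coverage of a nominal 95% interval = 2Φ(1.96 × 0.90) − 1 = 2Φ(1.764) − 1 ≈ 0.92.

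With n = 200 and p = 0.5, the 180 observed patients support a width of 2 × 1.96 × √(0.25/180) = 0.146. The filled data report 2 × 1.96 × √(0.9 × 0.25/200) = 0.131. That is narrower than 200 fully observed patients would give (0.139).

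**3. Cox models.** The article gives no effect sizes, event counts or expected missingness for these models, so the inputs are assumptions: n = 350 (largest row of Table 1); true exposure HR 1.00; one confounder with HR 2.01 per SD and latent correlation 0.5 with exposure, or HR 2.72 and 0.7; 10% of confounder values missing, either completely at random or depending on exposure and event. That makes four settings, with 400 replicates in one and 250 in each of the others. Multiple imputation used 5 or 10 imputations, with the event indicator and cumulative hazard in the imputation model. Ranges are over the four settings; the SE ratio is model SE over empirical SE.

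| Method | Exposure HR (true 1.00) | Coverage | Covariate HR (true 2.01) | Covariate HR (true 2.72) | Covariate coverage | Covariate SE ratio |
|---|---|---|---|---|---|---|
| Full data | 0.985–1.002 | 95–97% | 2.02–2.03 | 2.73–2.75 | 92–97% | 0.93–1.00 |
| Unconditional mean | 1.06–1.16 | 87–95% | 1.95–1.98 | 2.49–2.59 | 86–94% | 0.96–1.09 |
| Conditional mean, outcome not used | 0.98–1.00 | 96–97% | 2.01 | 2.68–2.71 | 94–96% | 0.95–1.04 |
| Conditional mean, outcome used | 0.92–0.96 | 90–96% | 2.14–2.16 | 2.94–2.96 | 86–89% | 0.88–0.96 |
| Multiple imputation | 0.99–1.01 | 96–98% | 1.99–2.00 | 2.61–2.66 | 94–95% | 1.01–1.18 |

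A separate simulation (n = 300, correlation 0.6, confounder HR 2 per SD, 400 runs) agrees in direction. Unconditional mean at 10% missing gave a null HR of 1.05–1.07 and type I error of 7–8%, against about 6% with full data.

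Monte Carlo error: with 250 replicates, a coverage near 95% has standard error √(0.95 × 0.05/250) = 1.4 points. The 87% figure is clearly below nominal; values of 93–95% are not.

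**4. The limit.** If a confounder over 10% were left out of the model, the exposure HR in the four settings would be 1.59–2.41, with coverage of 0–13%. This shows why the consequence must be fixed in advance. It does not describe a rule in the plan.

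**The case against.** **The list is illustrative.** The wording leaves the strategy open, and the Data analyses section foresees supplementary plans for specific questions, prognostic factors among them. That is fair, but those plans start from this general one, and an unsuitable method named as an example is still a poor default.

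**Three stronger readings are tempting, and the text does not support them.**

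- A reader might infer that confounders or patients above 10% are removed. The text states no unit and no action, and the selection rule never mentions missingness. The same sentence says that gaps are imputed, so large losses of patients cannot be attributed to it either.
- A reader might infer that every named method biases hazard ratios and shrinks standard errors. Conditional mean without the outcome was close to unbiased at 10%. Cox standard errors under unconditional mean were about right, because the filled rows add no spread in that covariate. Understated Cox standard errors appeared only when the outcome was used for a single fill-in.
- A reader might fault EM as such. EM as likelihood estimation is sound; the criticism applies only to single values filled in from it and then analysed as observed.

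**Missingness may stay low.** Collection lists shared with centres, fibrinogen and haemoglobin recorded at each event, and completeness checks reviewed by the coordination team all help. The article gives no expected missingness, so this cannot be settled. The harm shown here, however, arises within the 10% that the plan accepts.

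**The effect can be small.** At moderate assumed confounding, the excess type I error is hardly distinguishable from simulation noise. This stands; the size depends on the strength of confounding.

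**Conclusion.** The point holds in bounded form. Unconditional mean imputation should not be a named option for these models. At 10% missing it moved a null HR to about 1.05–1.16, with coverage of 87–95%. It is meaningless for categorical factors, and it brings nominal 95% intervals for simple means and proportions to about 92%. Single conditional-mean imputation using the outcome is also unsuitable: it raised the covariate's HR from 2.01 to 2.14–2.16, or from 2.72 to 2.94–2.96, with coverage of 86–89%.

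The 10% limit is undefined. Serious confounding would follow only if it were applied by dropping a confounder, which the text does not say.

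The Cox figures are illustrative and rest on the assumed correlation, confounder strength, sample size and missingness pattern. The 92% follows from algebra and needs only 10% missing completely at random. Multiple imputation was close to unbiased for the exposure. It slightly attenuated the covariate's HR in the stronger setting (2.61–2.66 against 2.72), with coverage of 94–95%.

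**What to change.** Replace the sentence on imputation and the limit with text to this effect:

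> Missing data will be handled by multiple imputation, pooled by Rubin's rules. The imputation model will contain all analysis covariates, treatment, the event indicator and the cumulative hazard, with a model suited to each variable type. Missingness above 10% in a variable triggers a query to the centres; it is not a reason to drop variables or patients. A complete-case analysis will be reported as a sensitivity analysis.

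The number of imputations can be set in the supplementary plans; at least 20 would be reasonable. If EM is kept, it should be used as a likelihood method with valid standard errors, not to fill in single values. The completeness reports described under Data quality checks can carry the 10% trigger.

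**Cost.** No new data and no change to the case report form, but some extra analysis work. The main burden is the federated design: data stay with each provider, and the Sample size section expects about 3–5 cases a year at many centres, too few for a separate imputation model at each. The plan must therefore say whether imputation runs on a pooled analysis set or through a federated procedure.

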#### Data quality checks

Data quality checks aim to assess whether data values are present, if they adhere to specific standard and if they are believable in terms of:

Conformance: the data should be recorded in agreement with the correct formats (e.g. range of values, date formats);

Completeness: the data should not have missing values or data records;Plausibility: the data should be believable (e.g. internal consistency; temporal and atemporal comparison);

Quality checks of the data conformance are included in the CRF in the form of predefined alerts and errors running during the data input. Moreover, several additional completeness and plausibility checks (e.g. completeness of variables for each patient, plausibility of temporal intervals between different dates, etc.) are implemented in an external web tool connected to the CRF by use of API key, capable of executing all data quality checks simultaneously. The API key is not transmitted outside the centre, it is used only locally to perform data quality checks. The results of these checks are available locally for each centre and periodically they will be summarized in reports that the registry coordination team (INT) will monitor and discuss with each centre.

#### Status and timeline of the registry

The registry initiated recruiting in December 2023. The estimated completion date is December 2033 upon agreement on the achievement of all the registry objectives. In order to promptly share with all the contributing centres and relevant stakeholders the progresses done by the EHE registry, the challenges encountered and observation derived from the analyses of patients included in the registry, especially if useful for clinical practice, yearly update meeting will be scheduled.

#### Ethics statement

In Europe, the processing of personal data for scientific research can be grounded upon several conditions of lawfulness, established in Article 9(2) of the General Data Protection Regulation (GDPR). Among these, the most relevant ones are:

the consent of data subjects (Art. 9(2)lit. a);the pursuing of a substantial public interest, on the basis of Union or Member State law (Art. 9(2)lit. g);the pursuing of a scientific research purpose on the basis of Union or Member State law (Art. 9(2)lit. j).

In addition, another possibility lies in the so-called “Compatibility Assessment”.

The GDPR allows or requires Member States to implement national specifications or derogations from certain rules set out in the GDPR, therefore the legal basis of the federated registry will be based in each participating hospital on the laws and regulations of its country.

If the legal basis of the registry is patient consent, this will be informed and written.

The EURACAN registry was approved by the Ethics Committee of the Fondazione IRCCS Istituto Nazionale dei Tumori, Milan.

## Discussion

The EHE prospective registry developed in the context of the EURACAN registry will be the first, international registry fully dedicated to an ultra-rare sarcoma such as EHE, which will serve as an example for other sarcomas and ultra-rare tumours. It has been developed with the support and in close collaboration with EHE patient’s associations (EHE Rare Cancer Charity UK) and it will foresee an extensive participation of sarcoma reference centers (22) mostly belonging to the EURACAN sarcoma domain across 10 EU countries and UK, with a concrete possibility in the near future of expanding this effort further across borders.

The current project recognizes several limitations. There is a risk of limited representativeness due to the hospital-based nature of the registry and to the involvement of sarcoma reference centers only. However, the representativeness of the registry will be tested by comparing registry data with population-based data in terms of relevant variables (e.g. age, stage, prognosis). Confounders could be another issue raising from the observational nature of the registry. Adequate statistics methods (e.g. marginal structural model) will be used in case of time-varying treatments/confounders and confounding by indication (selective prescribing). Directed acyclic graphs can also be useful to identify the source of bias and will be utilized in the definitions of the path between covariates. Also, the completeness of clinical follow-up could represent a problem but active research into the patients’ state of life will be guaranteed.

Despite the limitations described above, we believe that the establishment of this registry will represents a crucial step forward in the comprehension of EHE. The CRF developed for the registry, while containing the minimum dataset felt adequate for all sarcomas, has been entirely shaped for EHE, and will be able to captures all the peculiarities of this disease. The quality of the data collected within the registry will be ensured by the expertise of the joining centers but also by an agreed consistent practice in EHE management among participating clinicians, derived by the consensus paper from the worldwide sarcoma community focusing on this disease, and published in 2021. Furthermore, the semi-annual updates, while not necessarily guaranteeing the same follow-up time in each center, will increase the time windows with useful information to evaluate the time elapsed between events, increasing the quality of the data. Periodical call between the registry coordination team and the participating centers will be also scheduled to provide assistance with any possible issues which will arise in due course.

The data collected within the registry will provide a unique source on information to address some of the unresolved questions on EHE natural history, prognosis, management approach according to the different clinical scenario, treatment response and outcome. This will be instrumental for clinicians to better inform patients with EHE and tailor their treatment, but it will hopefully also provide a backbone to facilitate the development of clinical studies on new potentially active drugs and pave the way for the discussion with competent authorities for approval.
